# Effectiveness of a culturally tailored SMS alcohol intervention for same-sex attracted women: protocol for an RCT

**DOI:** 10.1186/s12905-019-0729-y

**Published:** 2019-02-06

**Keywords:** Alcohol, Intervention, Short message service (SMS), Same-sex attracted women, Lesbian, Bisexual, Women, Randomized controlled trial (RCT)

## Abstract

**Background:**

There is a large disparity between alcohol treatment access and prevalence of hazardous drinking among same-sex attracted women (SSAW). Yet, this population typically report low satisfaction with care and a reluctance to attend mainstream health services. Currently, there are few culturally tailored services for SSAW available despite evidence indicating that many feel uncomfortable in mainstream services. This paper describes the protocol of a randomised controlled trial aimed at examining the impact of a culturally sensitive four-week short message service (SMS) alcohol intervention on SSAW’s alcohol intake, wellbeing, and engagement with alcohol treatment.

**Methods:**

A randomised controlled trial comparing a culturally tailored SMS intervention (The Step One Program) with a generic ‘thank you’ message, and a nested qualitative study to further explore the intervention’s feasibility and acceptability. The Step One Program was co-designed using an Intervention Mapping framework and engaging potential consumers in the developmental process. Participants are block randomised (1:1 ratio) and followed up at the completion of the intervention and at 12 weeks post-intervention. The primary outcomes are alcohol reduction (as measured by the Alcohol Use Disorders Identification Test and self-reported alcohol intake), wellbeing (as measured by the Personal Wellbeing Index – Adult), and help-seeking (as measured by the number of alcohol services accessed and frequency of access). Upon completion of the 12-week post-intervention survey, participants in the intervention group were contacted via email regarding a phone interview on intervention acceptability.

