## Research objectives

### Hypotheses

Compared to participants who receive generic ‘thank you’ messages, participants in the Step One Program will report at the end of the intervention (4 weeks) and 12 weeks post-intervention:Significantly lower alcohol intake as measured by the Alcohol Use Disorders Identification Test (AUDIT) and self-report of number of standard drinks consumed in the previous 30 days.Significantly higher wellbeing as measured by the Personal Wellbeing Index – Adult (PWI-A).Significantly higher service engagement as indicated by the number of services accessed and frequency of access.

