##### Intervention development

The intervention was co-designed with potential consumers and utilised an Intervention Mapping framework [22, 23] which provides a best practice process to intervention development with a strong focus of engaging potential consumers in the developmental process. This consisted of six steps to develop an evidence-based intervention with each step being cumulative so that the result of each step guided the next ([name], [name], [name], [name], & [name]: Development of a tailored SMS alcohol intervention for same-sex attracted women using an intervention mapping framework, in preparation).

The first step involved a needs assessment to identify the gap in culturally tailored or appropriate alcohol treatment services available to SSAW. This included a comprehensive literature review and running focus groups with SSAW to explore whether they wanted a culturally tailored service and what they believed should be included. Step two involved developing a table of performance objectives (see Table 2) in which each cell of the table outlined what participants would need to learn or change in order to reduce their alcohol intake, improve their wellbeing, and increase their access to alcohol support services. The selection of these three primary outcomes was influenced by the literature and focus group discussions. Alcohol reduction was selected because research has consistently demonstrated a greater risk for hazardous alcohol use among SSAW compared to heterosexual women [3, 4, 24]. Wellbeing was selected as SSAW who drink hazardously also tend to have a lower level of general wellbeing as they commonly report experiences of sexual and physical abuse [25, 26], low social support [27, 28], and less access to housing, employment and healthcare [29–31]. Finally, help-seeking was selected as SSAW are typically reluctant to seek professional help due to a lack of services which are responsive to their unique needs [5, 8].

**Table 2 Tab2:** Table of Performance Objectives

Performance Objectives	Targets of Change			
	Resilience	Mental Health	Social Support	Motivation to Change

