### Power analysis

The target sample size is 50 participants per group. Assuming 20% attrition rate, we estimate to collect complete data from 40 participants in each group. Sample size calculations are based on the only available Australian study of alcohol consumption in this population, the Australian Alcohol and lesbian/bisexual women – insights into culture and emotions (ALICE) study [1], which provides estimates for the AUDIT score. A sample size of 40 participants per group has 84% power for detecting a post-intervention mean change of 4 points in the AUDIT score, when the standard deviation is assumed as 6 for two independent groups, two-tailed test, and significance level 0.05. This sample size will achieve 80% power to detect effect sizes larger than 0.63 for any of the other scores outcomes.

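### Three co-equal primary outcomes, carried by five measures at two time points, are planned at one undivided 0.05 with no ranking or success rule, so the false-positive rate is not held at 5%

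*Protocol article*

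**What the plan says.** The Abstract (Methods) gives the primary outcomes in three domains:

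- Alcohol reduction, two measures (AUDIT and self-reported intake): "The primary outcomes are alcohol reduction (as measured by the Alcohol Use Disorders Identification Test and self-reported alcohol intake), wellbeing".
- Wellbeing, one measure: "wellbeing (as measured by the Personal Wellbeing Index – Adult)".
- Help-seeking, two measures: "help-seeking (as measured by the number of alcohol services accessed and frequency of access)".

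Intervention development treats the domains as equals: "The selection of these three primary outcomes was influenced by the literature and focus group discussions". The Hypotheses expect a significantly better result on each measure, and "participants in the Step One Program will report at the end of the intervention (4 weeks) and 12 weeks post-intervention" applies to all of them.

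Data analysis fits a linear mixed model to each numerical outcome, with group, time (T1, T2, T3) and their interaction. It does not say which contrast or time point decides the result.

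Power analysis works with "two-tailed test, and significance level 0.05" and states: "A sample size of 40 participants per group has 84% power for detecting a post-intervention mean change of 4 points in the AUDIT score", with an SD of 6. It then claims 80% power for effect sizes above 0.63 on the other score outcomes.

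**The concern.** A trial that names several primary outcomes must either say which one decides, require all of them to succeed, or share the significance level among them. This article does none of these. It nevertheless fixes the two choices that create the problem: several co-equal primaries at two time points, and a sample size computed at an undivided 0.05.

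A reader of the final report could not tell whether one significant measure out of five, at one time point out of two, supports effectiveness. The stated power also gives no assurance about the primary question as a whole, because it is computed one comparison at a time.

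**Working it through.** **Inputs.** From Power analysis: 40 completers per group, AUDIT difference 4, SD 6, two-sided 0.05, 50 randomised per group, 20% attrition. From the Abstract and Hypotheses: five primary measures and two post-baseline time points. The document gives no correlations between measures or time points, so these are assumed and varied.

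**1. The plan's own figures.**

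- Completers: 50 × 0.80 = 40 per group.
- AUDIT: d = 4/6 = 0.667 and noncentrality 0.667 × √(40/2) = 2.98. Normal approximation: Φ(2.98 − 1.96) = 84.6%. Noncentral t on 78 df: 83.8%. The stated 84% reproduces.
- Other scores, d = 0.63: 80.4% (normal) or 79.5% (t). The stated 80% reproduces.

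**2. Number of tests.** If each outcome's model yields one group-by-time test, there are 5. If T2 and T3 are tested separately, as the Hypotheses are worded, there are 5 × 2 = 10.

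**3. Chance of at least one p < 0.05 when no true effects exist.** For independent tests this is 1 − 0.95^k: 1 − 0.95^5 = 22.6% and 1 − 0.95^10 = 40.1%. For correlated tests it was simulated with equicorrelated normal statistics (400,000 draws).

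| Assumed common correlation | 5 tests | 10 tests |
|---|---|---|
| 0 | 22.6% | 40.1% |
| 0.3 | 20.9% | 35.1% |
| 0.5 | 18.3% | 28.8% |
| 0.8 | 12.8% | 17.3% |

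A mixed pattern was also tried: AUDIT with drinks 0.6, the two service measures 0.8, other pairs 0.2, and 0.5 to 0.7 between time points. It gives 19.7% for five tests and 31–33% for ten. Even at a common correlation of 0.9 the rates are 10.2% and 12.8%.

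**4. AUDIT power if 0.05 were split by Bonferroni** (two-sample t, 40 per group).

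- Five measures, alpha 0.05/5 = 0.01: 63.4%. Restoring 84% needs about 60 completers, or 60/0.80 = 75 randomised, per group.
- Ten tests, alpha 0.05/10 = 0.005: 53.9%. Restoring 84% needs about 68 completers, or 68/0.80 = 85 randomised, per group.
- For the other scores, power at d = 0.63 falls to 57.2% and 47.6% respectively.

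**5. AUDIT power with one designated primary.** Alpha stays at 0.05, so 84% and 50 per group are unchanged.

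**The case against.** **The analysis plan may handle this.** Testing order and multiplicity method are often left to a SAP, which is not shown, and an article is condensed. That is a fair answer to a complaint about missing detail. It does not answer this one, because the article has itself fixed which outcomes are primary and the alpha used for sizing. A SAP that split alpha would undo the stated power, and one that chose a single primary would contradict the Abstract and Hypotheses.

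**Ten tests at 40% is too harsh.** This stands in part. A reader might infer that ten tests are prescribed, but Data analysis can equally be read as one interaction test per outcome. The 40% is also the ceiling for independent tests. AUDIT and 30-day drinks both measure drinking, the two service measures come from one list, and the same people answer twice. A range is the honest statement.

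**No rule says that any single success suffices.** This is correct. A reader might infer such a rule, but the Hypotheses join measures and time points without giving a success criterion. If all had to succeed, the error rate would not inflate, but joint power could not exceed that of the weakest outcome. The fault is that the rule is left open.

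**Power for other outcomes was considered.** This is also correct: the 0.63 sentence exists and reproduces. It is unadjusted too, and since it speaks of scores it does not clearly cover a count of services or frequency in ordered categories.

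**Error control need not cost power.** This stands. It is tempting to say that any later adjustment destroys the 84%, but a fixed sequence starting with AUDIT keeps AUDIT at 0.05.

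**AUDIT at T2 uses a different recall window from baseline.** According to Alcohol use and severity, questions 3 to 10 cover four weeks at T2 instead of a year. Both arms use the same window, so the between-group comparison at T2 remains valid.

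**Conclusion.** The concern holds in a limited form. Tested as the article is worded, with each primary measure at 0.05, the familywise error is about 13–23% for five tests and 17–40% for ten, roughly 2.5 to 8 times the nominal level. This range rests on assumed common correlations from 0.8 down to 0, with no true effect on any measure.

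The 84% is not a miscalculation. It describes one comparison, AUDIT post-intervention, at unadjusted 0.05. The fall to about 63% or 54% applies only if Bonferroni is chosen, and it uses a two-sample t approximation rather than the planned mixed model.

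The documents do not support saying that a 40% error rate is built in, that one success in ten is the declared criterion, or that the planned power is lost under every form of control.

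**What to change.** Before outcome data are analysed:

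- Name AUDIT at T2 as the single primary outcome, tested at two-sided 0.05 as the group contrast at T2 from the planned mixed model, accounting for T1. It is the natural choice because the sample size is computed for a post-intervention AUDIT difference and Data collection labels T2 as post-intervention.
- Make 30-day drinks, PWI-A, both help-seeking measures and all T3 contrasts secondary. Either test them in a fixed sequence after AUDIT or with Holm, or report them with confidence intervals and no confirmatory claim.
- Align the Abstract, Hypotheses, Intervention development and Power analysis with this choice, and update the registry entry if it differs.

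The planning figures of 84% power and 50 per group are kept. The work is wording, plus a registry update if needed. The real cost is that wellbeing and help-seeking can no longer be claimed as confirmatory findings in their own right.

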**Discussion:**

This study may have important implications for clinical practice, improve healthcare access and equity for SSAW, and provide direction for future research in this field. The outcomes of the current study may stimulate the development of other culturally tailored health programs for SSAW. The results will inform whether individually tailoring the messages according to content and delivery frequency may be warranted to increase its acceptability.

**Trial registration:**

This trial was registered with the Australian New Zealand Clinical Trials Registry (trial ID: ACTRN12617000768392).

## Background

Same-sex attracted women (SSAW) typically report low utilisation of alcohol treatment options [1] despite some evidence of higher levels of alcohol consumption than heterosexual women [2–4]. Research also indicates that many SSAW are reluctant to seek help for alcohol-related problems from mainstream clinical services as they report low satisfaction with their care, and have difficulty finding sensitive and appropriate services [5–8]. Such findings highlight the need for culturally tailored services that meet their specific needs, and increase equity and access to appropriate alcohol treatment. However, to our knowledge, no research has been published which examines interventions specifically for SSAW to facilitate alcohol reduction.

It has been suggested that problematic drinking among SSAW is often associated with stressors specific to their sexual identity or exacerbated by their sexual identity [5] and these stressors are typically revealed during the process of reducing or abstaining from drinking. Yet many health practitioners receive little or no lesbian, gay, bisexual, and transgender (LGBT) cultural sensitivity training, or education about LGBT health issues [9, 10], which means these significant issues are often not adequately addressed or considered [11].

eHealth services are gaining popularity, particularly with women [12], and emerging evidence indicates short message service (SMS) has the potential to assist individuals with reducing their alcohol intake. A systematic review of SMS interventions to prevent alcohol and substance abuse has been conducted [13]. Among the seven studies reporting feasibility and acceptability outcomes, six demonstrated evidence of both and one reported low acceptability [13]. Importantly, six studies included in the review demonstrated a significant reduction in alcohol use [13]. For example, Suffoletto and colleagues [14] explored the effectiveness of delivering alcohol-related assessments plus feedback via SMS to outpatients from four hospital emergency departments in the United States of America. Participants were randomised into three groups: receiving the weekly SMS drinking-related assessments plus feedback (group one, *n* = 384), receiving weekly SMS drinking-related assessment without feedback (group two, *n* = 196), or usual care (group three, *n* = 185). Participants in group one reported significantly less binge drinking days and drinks per drinking day while participants in groups two and three reported a significant increase on both measures [14].

SMS studies to date have not specifically targeted SSAW or LGBT populations. Rather, they have typically used mainstream samples of young adults or students [15–17]. To the author’s knowledge, one SMS study has specifically targeted a minority population of socially disadvantaged men [18]. Nonetheless, based on the available evidence, SMS appears to be an appropriate method for delivering a brief alcohol intervention to SSAW. In addition to being accessible and wide reaching [19, 20], it overcomes many commonly reported barriers preventing SSAW from seeking alcohol support. For example, studies using Australian community-based samples of SSAW have found a shared concern of feeling discriminated against or experiencing heterosexist attitudes from the health practitioner, fear of perceived stigma relating to their sexual orientation or fears of being judged for their alcohol use, and a concern that their sexual orientation will be pathologised [1, 6]. As well as overcoming help-seeking barriers, SMS interventions are potentially a safe starting point for SSAW who are considering reducing their alcohol intake but do not yet feel confident seeking face-to-face support.

In order to address the service gap for SSAW, we developed the *Step One Program*, which is a culturally tailored SMS intervention for SSAW. Although the term ‘tailored’ often refers to customisation for individuals, we will be ‘culturally tailoring’ the message content which Pasick, D’Onofrio, and Otero-Sabogal [21] have defined as “the development of interventions, strategies, messages, and materials to conform with specific cultural characteristics” (p. 145). The program aim is to facilitate alcohol reduction, improve wellbeing, and increase help-seeking among SSAW. The current paper describes the protocol for a randomised controlled trial (RCT) to evaluate the effectiveness of the Step One Program for SSAW, and the feasibility and acceptability of conducting an SMS intervention for SSAW.

## Research objectives

### Hypotheses

Compared to participants who receive generic ‘thank you’ messages, participants in the Step One Program will report at the end of the intervention (4 weeks) and 12 weeks post-intervention:Significantly lower alcohol intake as measured by the Alcohol Use Disorders Identification Test (AUDIT) and self-report of number of standard drinks consumed in the previous 30 days.Significantly higher wellbeing as measured by the Personal Wellbeing Index – Adult (PWI-A).Significantly higher service engagement as indicated by the number of services accessed and frequency of access.

## Methods

### Study design

A mixed methods approach was employed with a two-group, parallel, single-blind RCT, and a nested qualitative study to further explore the intervention’s feasibility and acceptability. The trial is registered with the Australian New Zealand Clinical Trials Registry (trial ID: ACTRN12617000768392). Ethics approval was obtained from the Deakin University Human Research Ethics Committee (reference number: 2017–077).

### Procedure

The study procedure described in the following sections is presented in Fig. 1.

**Fig. 1 Fig1:**
[figure not shown]
Procedure flowchart

#### Participant recruitment

Recruitment commenced April 24, 2017 and data collection is ongoing. Participants are recruited from four sources:General practice clinics across Australia that are known to have a high SSAW case-load;Nation- and State-wide SSAW community and social networks through email, websites, and social media. General women’s health groups are also contacted to reach SSAW not active in the LGBT community;Participants from the Rainbow Women’s Help-Seeking study (which examined professional and social help-seeking by SSAW) [7], and the ALICE study (which investigated socio-cultural factors which influenced alcohol use, sexual orientation, mental health, and health service use among SSAW) [1], with permission from the University of Melbourne;Public common areas, such as restrooms and community noticeboards.

Individuals enrol in the study by completing the online baseline survey using a link included with all study advertisements. The home page of the survey provides detailed information about the study, what participation involves, that participants can withdraw at any time and if so, they will be requested (but not obligated) to complete a survey containing the primary outcome measures, that it is anonymous, and that all information collected is confidential. It is a requirement to indicate consent before proceeding to the survey. To acknowledge the time taken to participate, participants who complete the final follow-up survey will go into a draw to win one of two $50 retail vouchers.

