#### Data collection

##### Baseline (T1)

Baseline data are collected using an online survey using *Qualtrics*. The survey primarily measures alcohol use, wellbeing, and current help-seeking. For a list of measures, please refer to Table 1. Participants are asked to provide their primary email address and mobile telephone number to send two follow-up surveys and to deliver the SMS intervention.

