#### Random allocation

Individuals are screened for eligibility. The first two eligibility criteria are determined in the baseline survey. If an individual responds that they identify as a man or they are aged under 18 years, they will be automatically directed to the end of the survey. The AUDIT score is calculated by [name] once the baseline survey is received. If the individual scores eight or above, they will then receive a welcome email and test SMS message. Once the receipt of both has been confirmed, participants are randomly allocated into the intervention group or the control group using a computer generated block randomisation at a 1:1 ratio with 10 allocations per block to ensure equal numbers in each group if the recruitment goal is not achieved. The sequence of condition allocations are placed in opaque envelopes with participant identification numbers on the front. Once a participant’s eligibility is determined, an envelope is opened by [name] and the participant is allocated to the experimental condition inside the envelope. As participants are blinded, to reduce bias they will not be informed of the number or frequency of messages in the intervention as this information will reveal which group participants have been randomly allocated to.

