#### Intervention group

The intervention consists of automated culturally tailored supportive SMS messages which are delivered through *MessageMedia*, an Australian SMS platform. It is designed to begin on a Monday and end on a Sunday. Messages are delivered daily for four weeks with two messages on Thursdays, Fridays and Saturdays, as people typically drink alcohol on these days (40 messages in total). Messages are sent at varying times between 3:00 p.m. and 4:30 p.m., and on days with two messages, the second is delivered between 6:00 p.m. and 8:00 p.m. On Sundays, the message asks participants to reply via SMS with the number of standard drinks they have consumed in the past seven days. In the welcome email, all intervention participants receive a standard drinks chart and an author-developed list of LGBT specific or friendly alcohol and mental health services.

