### Data analysis

All data will be de-identified and coded to ensure participant anonymity and it will stored securely on a password protected computer. Participant names, corresponding identification numbers, and contact information will be kept in a separate password protected file on a secure computer at Deakin University. Only the research team will have access to secured information. Only the de-identified data will be used in the analysis phase and in the summary of main outcomes that will be delivered to participants, any subsequent publications, and conference presentations. A data monitoring committee is not needed for this study as it is a non-therapeutic (behavioural) trial using low-risk procedures, and as such, the study team will be monitoring the data.

Analyses will be conducted using an intention-to-treat (ITT) approach [59], with all randomised participants analysed in their allocated group regardless of the intervention uptake. Every effort will be made to minimise missing data and where appropriate, multiple imputation will be used to handle missing data.

Baseline participant’s characteristics will be compared between the intervention and control group using Chi-squared or Fisher’s exact test for categorical variables, and *t* test or Kruskal-Wallis test for numerical variables. Drop-out bias will also be assessed using the same approach but comparing the baseline characteristics of participants with complete data against those lost to follow-up as a function of treatment group.

The intervention effect during the 12-week follow-up on numerical outcomes will be assessed using linear mixed models including group, time (T1, T2 and T3) and group by time interaction as fixed effects and participant as a random effect.

The feasibility of the Step One Program will be determined by the proportion of individuals who completed the baseline survey and were eligible to participate, how often participants read the SMS messages, how often they respond to Sunday SMS messages, and completion of follow-up surveys. Intervention acceptability will be reported by 1) summarising the multiple choice responses to the intervention acceptability questions in the T2 survey, and 2) performing qualitative analysis of the short answer responses and interviews using simple coding to identify recurring patterns and themes.

We will explore whether changes between T1 and T2 in the primary outcomes are correlated with changes in the potential mediator variables.

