## Discussion

SSAW tend to drink more than heterosexual women but are generally less likely to seek treatment [4, 24, 60, 61]. There are a range of barriers to SSAW accessing treatment [1], including a reluctance to attend mainstream clinical services, reports of low satisfaction with their care in these services, and difficulty finding services that are culturally tailored, sensitive and meet their needs [5–8]. Thus, an alcohol intervention that is culturally tailored and aware of issues specific to SSAW has the potential to increase access to support.

Few alcohol support services exist in Australia which are culturally tailored to SSAW or LGBT individuals. *Thorne Harbour Health* [62] run a therapeutic group for SSAW called *Drink Limits* and LGBT specific Alcoholics Anonymous (AA) meetings are available. However, limitations exist for many SSAW as these services are mainly urban based, and anonymity is reduced as the LGBT population is quite small. Thus, it is not surprising that in an Australian study exploring SSAW’s help-seeking preferences and behaviour (*n* = 1706), 55% of respondents reported that they use the internet for informal support [63]. SMS appears to be a viable option given research highlighting SMS as an effective method for delivering brief alcohol interventions in mainstream samples [13], as well as it overcoming many help-seeking barriers, including the option for anonymity, and broad access for women in both urban and rural locations.

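### The article says participants are told it is anonymous, but the design makes their data confidential, coded and re-identifiable by the research team

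*Protocol article*

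**What the plan says.** Participant recruitment (Protocol article) lists what the survey home page covers. Among the items is "that it is anonymous, and that all information collected is confidential". The next sentence makes consent depend on that page: "It is a requirement to indicate consent before proceeding to the survey".

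Other sections describe how data are handled:

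- Baseline (T1): "Participants are asked to provide their primary email address and mobile telephone number to send two follow-up surveys and to deliver the SMS intervention".
- Random allocation: a team member scores the AUDIT from the returned survey, and then "If the individual scores eight or above, they will then receive a welcome email and test SMS message".
- Intervention group: messages go out through a named SMS platform, and on Sundays "the message asks participants to reply via SMS with the number of standard drinks they have consumed in the past seven days".
- Data analysis: "Participant names, corresponding identification numbers, and contact information will be kept in a separate password protected file". The same section says that all data are de-identified and coded, gives anonymity as the purpose, restricts access to the research team, and uses only de-identified data for analysis and reporting.

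**The concern.** Anonymous data cannot be traced to a person by anyone. Confidential data can be traced, but only by those entitled to do so. The reported page gives both assurances side by side, so the first cannot easily be read as a loose synonym for the second. The handling described elsewhere fits the second and not the first.

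What is at stake is an accurate account of the privacy risk people accept when they consent. The linked answers cover sexual and gender identity, hazardous drinking, depression, anxiety and stress scores, and use of services including police. The Background and Discussion cite fear of stigma and judgement, over sexual orientation and over drinking, as a barrier to seeking help in this population, and the Discussion counts the option of anonymity among the attractions of SMS. On the article's own account, then, whether participation is anonymous could bear on the decision to join.

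**Working it through.** No formula applies and the plan states no figure to reproduce. The check sets what anonymity would require against what each section describes.

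| Step | What the article describes | Compatible with anonymity? |
|---|---|---|
| Enrolment (Baseline T1) | Email address and mobile number requested | No, these are direct identifiers |
| Screening (Random allocation) | The AUDIT score from the survey decides who is emailed and texted | No, an answer is tied to contact details |
| Eligibility criteria | A reply to both the email and the test SMS is required | No, nobody can be randomised without being reachable |
| Intervention group | Weekly drink counts returned by SMS | No, a reply comes from the participant's phone |
| Post-T3 interview (Abstract, Methods) | Intervention participants emailed about a phone interview | No, it needs a retained address linked to allocation |
| Data analysis, storage | Names, identification numbers and contact details in a separate file | No, this is a re-identification key |
| Data analysis, model | Participant as a random effect over T1, T2 and T3 | Needs a within-person link; here the surveys are emailed to known addresses |

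The safeguards in Data analysis are coding, a separate password-protected key, access limited to the research team, and de-identified data for analysis, the summary to participants, publications and presentations. Each of these supports confidentiality. None removes the key, so none makes the data anonymous.

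The wording in Participant recruitment does not make clear whether the study, taking part, or a survey is said to be anonymous. Reading it as the study or taking part, the table settles the matter. Reading it as the survey, the baseline survey is where contact details are sought and the later ones are emailed to individuals, so the conclusion is the same.

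Reach, from the article's figures:

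- Planned participants: 50 per group × 2 groups = 100.
- Sunday replies: one per week × 4 weeks = up to 4 for each of the 50 planned intervention participants.
- People who gave contact details but scored below eight on the AUDIT: also affected, number not stated.

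One inference is needed. The article says the intervention messages are delivered through the platform. That the Sunday replies return the same way is the natural reading but is not spelled out.

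**The case against.** The strongest reply is that nobody reviewing the article has seen the consent page. Participant recruitment gives a short paraphrase in a condensed paper, and says the page gives detailed information on what taking part involves. The page may already explain the identification number, the platform and the de-identification. This stands. It limits what can be said about what participants were told, and it makes any correction of the page conditional. It does not rescue the article, which itself reports the word and contradicts it.

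A second reply is that the authors use the term loosely, since Data analysis treats coding as the route to anonymity, and that the safeguards are real. The safeguards stand and reduce the practical risk. The loose usage explains the slip but leaves the description wrong in two places.

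A third is that participants type in their own email and mobile number and must answer an email and an SMS before allocation, so they know they can be contacted. This also stands, and it tells against any suggestion of concealment.

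Several stronger inferences are tempting but unsupported:

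- A reader might infer that every participant was misled about disclosure. The unseen page prevents that conclusion.
- A reader might cite the Discussion's remark that "anonymity is reduced as the LGBT population is quite small" as an admission about this trial. It describes existing support services.
- A reader might take stigma to be this population's main fear. The Background lists it among several concerns and does not rank them.
- A reader might infer confusion over who would act on a worrying answer. No section addresses what participants assume about that.
- A reader might take the 4 + 12 = 16 weeks from the start of messages to T3 as a measure of risk. It is only the length of follow-up.

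**Conclusion.** The point holds as a wrong description of identifiability. The article attributes anonymity to a design that cannot run without linking people to their answers. It does so in Participant recruitment, as something told to people before consent, and again in Data analysis. The accurate description is confidential, coded and re-identifiable by the research team.

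The size is one property wrongly stated in two sections. It reaches all 100 planned participants and an unknown number screened, on the assumption that the page reads as the article reports. No breach or unprotected data flow is shown. A reader might suppose that identifiers stay with the answers until analysis. Data analysis does not say so: it has all data coded and the key held separately. Sample size, power and the effect estimate are untouched. The correction is worth making because the data are sensitive and the change costs almost nothing.

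**What to change.** 1. In Participant recruitment and Data analysis, replace the references to being anonymous and to anonymity with wording such as: *confidential, coded and re-identifiable by the research team, with only de-identified data used for analysis and reporting*.
2. State that the messages and the Sunday replies pass through the SMS platform, after confirming the route of the replies.
3. Check the actual participant information. If it already explains the link, nothing more is needed. If it says anonymous without this explanation, correct it and notify those already enrolled, since the article says data collection is ongoing.

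The cost is a text change in two sections and a check of one page. If the page is at fault, add an amendment to the participant information and one email to enrolled participants. The small downside is that a few people may decline once told that the team can identify them.
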